## 5. Study design

This is a double-blind, randomized, placebo-controlled superiority trial. Eligible subjects will receive either “CRF” granules or placebo granules for 8 weeks followed by a post-treatment visits at week 12.

## 6. Study population

COVID-19 recovered patient with a confirmed diagnosis of SARS-Cov-2 infection using the PCR or rapid antigen test according to the standard of Center for Health Protection, Department of Health, Hong Kong and released from isolation^1^ will be screened for the following eligibility criteria. Study subjects will be recruited from the following clinics/Chinese medicine centers: (1) The CUHK Chinese Medicine Specialty Clinic and Teaching and Research Center on CUHK campus (CUHK-CMSCTRC); (2) The two Integrative Medical Centers, Hong Kong Institute of Integrative Medicine at Shatin and Wan Chai. Moreover, patients following up for residual symptoms at the medical clinics at Prince of Wales Hospital will be provided our study information; interested patients can go to our Integrative Medical Center located at the same hospital. Advertisements in the poster on the clinic and internet platforms, such as Facebook, emails, and website will be made to facilitate community recruitment. Besides, we will publish articles in local newspapers and magazines as well as organize health promotion talks to augment the subject recruitment process.

### 6.1. Inclusion criteria

•Aged above 18.•Have fatigue and one more residual symptoms (e.g., dyspnoea, sleep disturbance, cough, loose stool, abdominal distension, loss of appetite, dizziness, etc.) at least 5 weeks after discharge.•Patients are diagnosed with “lung-spleen qi deficiency” and/or“dual deficiency of qi and yin” by a Chinese Medicine Practitioner.•Voluntary written consent.

### 6.2. Exclusion criteria

•Still being SARS-CoV-2 positive.•Known severe medical conditions, such as cardiovascular, liver or renal dysfunction, diabetes mellitus, cancers, cerebrovascular diseases, and blood system diseases.•Impaired hematological profile and liver/renal function.•No concomitant non-steroidal anti-inflammatory drugs (NSAIDs), steroids, antibiotics, prebiotics, and probiotics within 4 weeks.•Known allergic history to any Chinese herbal medicines;•Known pregnancy or lactating.

## 7. Patient visit

### 7.1. Screening visit

Subjects will be invited to come for screening. Information about the study will be explained and subject will sign the informed consent form before screening. Symptom assessment will be done to confirm if the subjects still have residual symptoms of fatigue and more such as dyspnoea and insomnia. Less than 10 ml blood for hematology, liver and renal function tests will be done as safety measures. A deep throat saliva/professional-administered combined nasal and throat swab test for SARS-CoV-2 will be arranged by using the accredited laboratory or Government service.

### 7.2. Baseline randomization visit

At randomization visit, eligible subjects will have medical consultation and assessment by registered Chinese medicine practitioners (CMPs) investigators. Vital sign will be assessed, medical history and concomitant medications will also be recorded. If the subject has a result of not detected or negative result of SARS-Cov-2 RT-PCR test of deep throat saliva/professional-administered combined nasal and throat swab, and negative medical and travel history related to COVID-19 within 72 h, subjects will be instructed to do a pulmonary function test using a designated spirometer and complete the questionnaires; however, performing deep throat saliva/professional-administered combined nasal and throat swab test and pulmonary function test are not mandatory. Subjects will be randomly assigned (in a 1:1 ratio) to receive 8 weeks of either “CRF” granules 23–42 g daily or placebo granules 23–42 g daily. CMP investigators will prescribe and dispense the study treatment accordingly.

### 7.3. Follow-up visit

Subjects will return for follow-up at week 8 (±4 days), and followed by a post-treatment visit at week 12 (Table 1). Symptom assessment and other questionnaires will be done. Blood tests will be repeated as safety measures at week 8. Subjects will be arranged to have another SARS-Cov-2 RT-PCR test of deep throat saliva/professional-administered combined nasal and throat swab, and confirmed to have negative medical and travel history related to COVID-19 within 72 h before the pulmonary function test at week 8. Performing deep throat saliva/professional-administered combined nasal and throat swab test and pulmonary function test are not mandatory. Treatment compliance will be recorded and adverse events will be captured on a patient diary. A direct telephone line will be provided so that subjects can report any adverse events during office hours between scheduled visits. The subjects will be recommended to attend Emergency Department at the nearest hospital beyond office hours if deemed necessary. To monitor compliance, subjects will be asked to bring back all remaining packs of granules for counting. One time free consultation with 1 month Chinese herbal treatment will be provided to all subjects after completion of study to ensure the follow up visit compliance.

**TABLE 1 T1:** Study schedule.

Items	Screening	Treatment period		Post-treatment follow up
	≤7 days to 0 day	Day 0 (baseline)	Week 8 (±4 days)	Week 12 (±4 days)
Informed consent	X			
Eligibility	X	X		
Medical consultation and assessment		X	X	X
Medical history		X		
Concomitant medication		X	X	X
Blood for safety measures	X		X	
Deep throat saliva or nasopharyngeal swab for SARS-Cov-2 RT-PCR test	*X		*X	
AE/SAE assessment			X	X
Questionnaires		X	X	X
Pulmonary function test		^#^X	^#^X	
Administration of study drug		X	X	
	

*Subjects will have deep throat saliva or nasopharyngeal swab for SARS-Cov-2 RT-PCR test within 72 h before follow up visit but it is not mandatory.

^#^Pulmonary function test will be skipped if no deep throat saliva has been done and showed not detected or negative within 72 h.

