## 10. Sample size and statistical methods

### 10.1. Sample size calculation

The primary outcome is Fatigue Severity Score (FSS). There is no any previous study on the Chinese medicine treatment of COVID-19 measured by FSS. The clinically meaningful improvement in FSS was assumed to be a drop of 9 out of 63 based on previous studies (33, 34). Based on the standard deviation of symptom score of residual fatigue in this study on COVID-19 recovered patients (33, 35), we assumed standard deviation estimates of 12. To detect a clinically meaningful difference of 9 points in FSS, sample size of 58 was estimated based on standard deviation estimates of 12 at an alpha of 0.05 and power of 0.8. It should be noted that these estimates are considered vague approximations, and 58 participants is a conservative estimate to detect a statistically significant result of change in FSS. To compensate a possible drop-out rate of 15%, totally 68 patients will be needed, with 34 in each group.

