### 10.2. Statistical analysis

Baseline data (gender, age, and vital signs) will be descriptively summarized. Differences of measurement data between the groups will be assessed using *t*-test for normally distributed continuous variables and Wilcoxon signed rank test for non-normally distributed variables. Measurement data of different groups in each visit will be reported as mean ± standard deviation (SD). Intra-group comparisons between baseline and each visit will be conducted by using paired *t*-test (or Wilcoxon signed rank test). Comparisons between groups will be conducted by using an analysis of variance (ANOVA), with other confounding factors like multicenter character conducting the covariate analysis. Statistical analysis for the data which do not meet above conditions (e.g., non-normal) will be conducted with the use of non-parametric test. For laboratory parameters, Spearman’s coefficient correlation has been used for comparison with different parameters and one way ANOVA test for significant correlation between groups. Study flow chart and graphs will be presented over different study times.

All *p*-values and 95 percent confidence intervals are two-sided, and *p* < 0.05 is considered statistically significant. Statistical analyses will be carried out exclusively by an independent statistician. All analyses will be performed by using SPSS, version 24 (SPSS).

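### Spirometry is optional separately at Day 0 and week 8, so summaries and between-arm comparisons of lung function can rest on different self-selected patients, and a Table 1 footnote contradicts the text on who is tested

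*Protocol article*

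**What the plan says.** **Outcome.** Section 4.2, item 5, lists improvement of FEV1, FVC and FEV1/FVC at week 8 as a secondary outcome.

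**Collection.** Section 7.2 directs patients with a negative SARS-CoV-2 result to do spirometry at Day 0, but adds that "performing deep throat saliva/professional-administered combined nasal and throat swab test and pulmonary function test are not mandatory". Section 7.3 repeats this for week 8: "Performing deep throat saliva/professional-administered combined nasal and throat swab test and pulmonary function test are not mandatory". Neither section links the two choices.

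**Which specimen qualifies.** Three wordings are in force:
- Sections 7.1 to 7.3 accept saliva or a combined swab. For week 8: "Subjects will be arranged to have another SARS-Cov-2 RT-PCR test of deep throat saliva/professional-administered combined nasal and throat swab".
- The Table 1 row and its asterisk footnote name a different swab: "Subjects will have deep throat saliva or nasopharyngeal swab for SARS-Cov-2 RT-PCR test within 72 h before follow up visit but it is not mandatory".
- The Table 1 hash footnote names saliva alone: "Pulmonary function test will be skipped if no deep throat saliva has been done and showed not detected or negative within 72 h".

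**Analysis.** Section 10.2 states "Measurement data of different groups in each visit will be reported as mean ± standard deviation (SD"). It then plans a within-group test: "Intra-group comparisons between baseline and each visit will be conducted by using paired" t-test, or the signed rank test. Arms are compared by ANOVA with covariates for confounders such as centre. The Day 0 value is not named as a covariate. Graphs over study time are also planned.

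**The concern.** Improvement can be measured only in a patient tested at both visits. With two unlinked choices, a patient may be tested at Day 0 only, at week 8 only, at both or at neither. The week-8 choice comes after eight weeks of treatment, when patients know how they feel.

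Two things are at stake. First, a week-8 mean set beside a Day 0 mean can differ because different people were tested. Second, a between-arm comparison of week-8 values is no longer protected by randomisation if willingness to be tested depends on breathlessness or perceived benefit and these differ by arm. That comparison is the one a placebo-controlled superiority trial relies on.

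The hash footnote is a separate fault with the same effect. Read literally, a patient whose only negative result came from a swab is skipped, although section 7.2 says that patient is to be tested. Sites that follow different sentences would test different patients.

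**Working it through.** **1. The plan's own figure.** No sample size is given for spirometry. The only calculation is for the Fatigue Severity Score (FSS) in section 10.1: "sample size of 58 was estimated based on standard deviation estimates of 12 at an alpha of 0.05 and power of 0.8". With a difference of 9 and an SD of 12, the standardised difference is 9/12 = 0.75.
- Normal approximation: 2 × (1.96 + 0.84)² / 0.75² = 27.9, so 28 per arm.
- t-distribution: 28.9, so 29 per arm and 58 in total. This matches the plan.
- Dropout: 58/0.85 = 68.2, against a stated 68.

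I therefore take 29 completers per arm.

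**2. How many have both tests.** Uptake u is assumed, and equal at both visits. Among 29 completers per arm:
- tested at week 8 = 29u
- both tests, independent choices = 29u²
- tested at week 8 with no Day 0 test = 29u(1 − u), a share of 1 − u of week-8 tests
- possible range for both tests, whatever the dependence = 29(2u − 1) to 29u, for u of at least 50%

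| Assumed u | Tested at week 8 | Both tests, independent | Possible range | Week-8 tests without Day 0 |
|---|---|---|---|---|
| 80% | 23.2 | 18.6 | 17.4 to 23.2 | 20% |
| 70% | 20.3 | 14.2 | 11.6 to 20.3 | 30% |
| 60% | 17.4 | 10.4 | 5.8 to 17.4 | 40% |

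At the upper end of each range the same patients opt in twice and the two sets coincide.

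**3. What the smaller numbers can detect.** For a two-sample t-test (two-sided alpha 0.05, power 0.8), the detectable difference is 0.75 SD with 29 per arm and 1.10 SD with 14 per arm. The SD is that of whatever quantity is compared. Adjusting for the Day 0 value would reduce it.

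**4. Which planned outputs are exposed.**
- Per-visit mean and SD, and graphs: exposed, because no restriction to patients tested twice is stated.
- Between-arm ANOVA: exposed if applied to week-8 values. Section 10.2 does not say whether values or changes are compared.
- Within-group paired test: not mixed, because it uses only patients with both values. It is still limited to those who opted in twice.

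**5. The specimen wording.** Take a patient with a negative combined swab within 72 h, no saliva sample and a clear medical and travel history. Section 7.2 says to test. The hash footnote says to skip. Both are current text, so this is a contradiction and not a gap that an analysis plan could fill.

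**The case against.** The strongest reply is that testing is the default. Patients are directed to do spirometry at Day 0, the week-8 swab is to be arranged for them, and Table 1 schedules the test at both visits. Optional may mean no more than a right to decline. The baseline-to-visit test is paired, the analysis set may be defined in a plan that is not shown, and the hash footnote looks like shorthand. Most of this stands, and it limits the point in three ways.

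- **A reader might infer that the two visits will cover different patients.** The documents permit this but do not make it happen.
- **A reader might infer that changing participation will pass for a treatment effect.** If week-8 uptake rises with FEV1 (assumed odds ratio 1.5 to 3 per SD, uptake 60% to 70%) and nothing truly changes, the mean of those tested at week 8 shifts by 0.12 to 0.35 SD. That applies only to unpaired visit means and graphs, and under this model it is equal in both arms. Between-arm bias needs uptake to depend on outcome differently by arm. In a double-blind trial that is possible, but nothing in the documents shows it.
- **A reader might treat the gain in precision from using each patient's Day 0 value as a cost of optional testing.** That gain exists at full uptake too. It is a reason to adjust, not evidence of harm from the visit rules.

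What the reply does not remove: an analysis plan cannot recover tests that were never done, a paired test within each arm does not replace the comparison between arms, and the footnote still contradicts section 7.2.

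**Conclusion.** The point holds in a limited form. Two unlinked optional tests, the second after randomisation, allow the per-visit means, graphs and any between-arm comparison of week-8 lung function to rest on different self-selected patients. They also confine the paired test to patients who opted in twice. Under assumed independent uptake of 80% to 60%, that is about 19 down to 10 of 29 completers per arm. The true number depends on uptake and on how far the two choices go together, and the documents give neither. The contradiction in Table 1 needs no assumption.

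One secondary outcome is affected. The primary FSS outcome and its sample size are not. The changes are worth making because they are cheap.

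**What to change.** 1. **Specimens.** Reconcile the Table 1 row, both Table 1 footnotes and sections 7.1 to 7.3, so that one list of qualifying specimens applies throughout. The sponsor must decide which list that is.
2. **Week-8 test.** State in section 7.3 that the week-8 swab and spirometry are scheduled for every patient with a Day 0 test, whatever their symptoms, with the right to decline kept.
3. **Analysis.** In section 10.2, compare arms on the week-8 value adjusted for the patient's own Day 0 value, in place of an ANOVA that does not name it. Base change summaries and graphs on patients with both tests, and report by arm how many had both.

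The cost is wording in sections 7.1 to 7.3, Table 1 and section 10.2, with no new procedure and no extra patients. The downside is that tests done only at week 8 do not contribute. Patients may still refuse at week 8, so some selection after randomisation remains. The counts by arm would make it visible but would not remove it.

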### 7.4. Study assessments

#### 7.4.1. Fatigue severity score (FSS)

Fatigue severity score is a 9-item scale which measures the severity of fatigue and its effect on a person’s activities and lifestyle in patients with a variety of disorders. Scores range from 9–63; the higher the score, the greater fatigue severity (23).

#### 7.4.2. Self-reported COVID-19 long term symptom assessment

For the symptom questionnaire, participants will be asked to report newly occurring and persistent symptoms, or any symptoms worse than before COVID-19 development. The symptom assessment has 5 scale, from none to very severe.

#### 7.4.3. The modified British medical research council (mMRC) dyspnoea scale

The mMRC scale is a five-category scale to characterize the level of dyspnoea with physical activity in which higher scores correspond with increased dyspnoea (6).

#### 7.4.4. EuroQol five-dimension five-level (EQ-5D-5L)

The EQ-5D-5L is a validated questionnaire to evaluate patient quality of life by assessment of the following five domains: mobility, self-care, usual activities, pain or discomfort, and anxiety or depression. Categorization within each factor is divided into five-levels that range from no problems to extreme problems (6). EuroQol Visual Analogue Scale (EQ-VAS) is a patient’s subjective assessment of generic health ranging from 0 (worst imaginable health) to 100 (best imaginable health) before COVID-19 and at the time of the visit, with higher scores representing better subjective health experience. A difference of 10 points defined worsened quality of life (6).

#### 7.4.5. Pulmonary function test device

FEV1, FVC, and FEV1/FVC ratio will be measured with the Air Next Spirometer (NuvoAir, Sweden) in combination with the mobile coaching system. Air Next is a novel spirometer that connects *via* bluetooth to a smartphone application, permitting patients to monitoring lung function at home. It has a turbine mechanism (Flow Mir) to perform measurements inside the disposable single use nozzles. To perform spirometry, the user exhales air into the turbine. This air turns a motor, and the device registers the speed of the rotor, adapts it, and transfers the data to the smartphone application (24). The higher of FEV1/FVC ratio, the healthier of subjects.

#### 7.4.6. Blood test

Venous blood samples will be collected from all participants for hematology, liver and renal function tests as safety measures.

#### 7.4.7. Subject withdrawal

A subject must be withdrawn from the study if he/she withdraws consent. Subjects who (1) experience adverse events, or (2) have pre-existing violation of entry criteria may remain in the study unless the investigator determines that it is not in the subject’s best interest to continue. The specific reason for withdrawal should be indicated.

Subjects who have withdrawn from the study will be invited to follow up at the last study visit i.e., 8 weeks after the randomization visit to detect any delayed clinical events.

## 8. Study intervention

### 8.1. Study treatments

The core study treatment, COVID Rehab Formula “CRF” is prepared in the form of mixed LJZD and SSMDD concentrated herbal granules with variations.

Essentially, the “CRF” consists of Ginseng Radix Et Rhizoma (renshen) 8 g, Atractylodis Macrocephalae (baizhu) 7.2 g, Rhizoma Poria (fuling) 7.2 g, Glycyrrhizae Radix Et Rhizoma Praeparata Cum Melle (zhigancao) 4.8 g, Glycyrrhizae Radix Et Rhizoma (gancao) 4 g, Pinelliae Rhizoma Praeparatum (fabanxia) 9.6 g, Citri Reticulatae Pericarpium (chenpi)7.2 g, Adenophorae Radix (nanshashen) 8 g, Polygonati Odorati Rhizoma (yuzhu) 8 g, Mori Folium (sangye) 4.8 g, Ophiopogonis Radix (maidong) 8 g, Lablab Semen Album (baibiandou) 8 g, and Radix Trichosanthis Radix (tianhuafen) 8 g.

For study subjects with the following symptoms, specified Chinese medicine will be added; fatigue: Astragali Radix (huangqi) 15 g; dyspnea or cough with sputum: Trichosanthis Pericarpium (gualoupi) 10 g, Fritillariae Thunbergii Bulbus (zhebeimu) 10 g, Armeniacae Semen Amarum (kuxingren) 10 g; sleep disturbance: Ziziphi Spinosae Semen (suanzaoren) 10 g, Indian Bread with Pine (fushen) 10 g and Margaritifera Concha (zhenzhumu) 10 g; loose stool: Plantaginis Semen (cheqianzi) 10 g, Artemisiae Scopariae Herba (mianyinchen) 15 g, and Coicis Semen (yiyiren) 10 g.

Granules will be used with the dosage equivalent to the raw herbs according to the manufacturer. One daily dose of which (weight 23–42 g) will be dissolved in hot water and administered while it is lukewarm. Study subjects will take 2 times daily, 1–2 packs in the morning and the other in the evening after meal. The placebo granules, made of starch and caramel with similar appearance, smell and taste to the CRF but contain no active constituents, will be taken by the patients in the placebo group in the same way as those in the treatment group.

Both treatment herbal and placebo granules will be produced by a manufacturer with a Good Manufacturing Practice (GMP) certificate.

### 8.2. Prohibited drugs

Non-steroidal anti-inflammatory drugs (NSAIDs), steroids and antibiotics are prohibited. Chinese medical treatments which are used to treat those residual symptoms are prohibited during the study period.

### 8.3. Treatment compliance

Treatment compliance is assessed by the number of doses taken during study period by subjects’ self-report and research personnel’s counting of returned packs of granules.

### 8.4. Randomization and blinding

A computer-generated randomization schedule is used to assign subjects to the treatment sequences. Concealment of allocation will be ascertained by an independent research staff member, and identically designed treatment packs will be used for study drugs.

This is a double-blind randomized controlled trial. The random allocations will be put into opaque envelops with sequential study numbers. Two sets of the envelope will be prepared, with one set for randomization at the site, and another set for storage in the investigator’s office for emergency un-blinding.

## 9. Possible risks and adverse event reporting

### 9.1. Possible risks and discomfort

In general, there will be minimal discomfort in blood taking and the risk include bleeding, infection, bruising, and feeling lightheaded. Besides, no serious adverse event has been reported in both decoction (25, 26) and their variations such as Indian Bread with Pine, Ziziphi Spinosae Semen and Margaritifera Conch (27).

There is mild discomfort of taking Shashen Maidong Decoction, Plantaginis Semen and Artemisiae Scopariae Herba including feeling of abdominal discomfort, diarrhea, abdominal distension, nausea, and vomiting as well as loss of appetite (28, 29). On the other hand, studies show that Fritillariae Thunbergii Bulbus may cause toothache, hand numbness and induce allergy reaction, but those can be relieved after treatment (30). Astragali Radix are found to induce allergy reaction, painful sensation on limbs, headache, insomnia and abdominal discomfort, but those may due to overdose usage (over 30 g) and using injection dosage form (31), while Trichosanthis Pericarpium are found to cause allergy reaction and abdominal discomfort, those are possibly by using injection dosage form (32). However, there is no documented evidences about possible risks and discomfort for Coicis Semen and Armeniacae Semen Amarum. Moreover, according to reports of interaction of CM and Herbal Medicine(s) with Anti-cancer Drugs forms, published by The University of Hong Kong, Department of Pharmacology and Pharmacy, there is no evidence for AE or harmful interaction between COVID-19 Rehabilitation Formula (CRF) and western medicine.

